### Assessment of Current Food Consumption by Applying the Software GloboDiet (24-Hour Recall) and Calculation of Energy and Nutrient Intake

During the second visit to the study center, the food consumption of the participants was assessed face-to-face by trained interviewers using the software GloboDiet. The software was adapted to the current German food market and modified for use in the German National Nutrition Monitoring of the adult population. The structure and standardization procedures of GloboDiet have been described in detail elsewhere [24]. For the 24-hour recall, participants were asked in detail about their food and beverage consumption, as well as the use of dietary supplements on the previous day. Corresponding to a first so-called quick list of the consumed foods and beverages in chronological order of the meals, the reported food items were further described by facets and descriptors (eg, the applied preparation method, the preservation method, the flavor, and the fat content). Consumed quantities were assessed with a picture book, household measurements, as well as standard units. Interviews were conducted on Mondays, Wednesdays, and Thursdays, leading to results of food consumption on Sundays, Tuesdays, and Wednesdays, representing a balanced coverage of weekdays and weekends, which was intended regarding the validation of the GloboDiet software.

Based on the assessed food consumption, energy and nutrient intake were calculated using data from the German Nutrient Database version 3.02 [31].

### Acquisition of Habitual Diet (30-Day Food Frequency Questionnaire)

The 48-item food frequency questionnaire (FFQ) that was used in this study is an adapted version of the validated 53-item FFQ applied in the German Health Examination Survey for Adults 2008-2011 [32]. The ErNst FFQ, therefore, includes questions on the frequency and amount of food groups consumed during the past 4 weeks. The questionnaire was given and explained to the participants on their second visit to the study center, with the request to complete it at home and return it. Frequencies for the consumption of food items were asked according to prespecified categories: never, once a month, 2-3 times a month, 1-2 times a week, 3-4 times a week, 5-6 times a week, 1 time per day, 2 times per day, 3 times per day, 4-5 times per day, and more than 5 times per day. Furthermore, participants had to report the portion sizes of the food items consumed in predefined answering categories. Portion sizes were based on common household measures such as a cup, a glass, a tablespoon, and so on, and, where applicable or necessary, supported by pictures to aid participants in estimating their usual intake. Habitual nutrient intake was calculated using the German Nutrient Database version 3.02 [31].

### 24-Hour Urine Collection

The 24-hour collection of urine by the study participants took place the day before the 24-hour dietary recall (visit 2). The study participants were provided with 2 urine collection containers (volume 2 liters, Sarstedt AG & Co) and were asked to store the urine at home in the refrigerator or in a cool bag with prechilled thermal packs to keep the collected urine permanently cool. This cool bag was also used to ensure the chilled transport of the urine collection until delivery to the study center. Urine collection was performed according to a standard protocol. On the first visit to the study center, participants were instructed by a study nurse and were given a protocol with written instructions and documentation. Subjects were interviewed about any difficulties during 24-hour urine collection on the second visit day (delivery of 24-hour urine). Urine samples were excluded from the analysis in case of collection errors, for example, if the collection time was interrupted, incomplete, or less than 20 hours, or if the first-morning urine was not discarded as described in the standard protocol.

Creatinine was analyzed as a reference value for potential urinary analytes using a method modified from Slot [33] and Heinegård and Tiderström [33,34] with the Urinary Creatinine Detection Kit from Arbor Assays (Ann Arbor) according to the manufacturer’s protocol. The creatinine excretion in urine was also used to estimate the completeness of the urine collection. Creatinine is formed during the breakdown of creatine or creatine phosphate. This occurs almost exclusively in muscle tissue; therefore creatinine excretion in the urine is related to muscle mass or fat-free body mass. Since creatinine excretion in urine is subject to intraindividual fluctuations and depends on the creatine or creatinine content of food [35], it is only suitable for a rough estimate of the completeness of the 24-hour urine collection.

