#### Nitrogen Content

Total urinary nitrogen was quantified by the Kjeldahl method using automated digestion and distillation units (Digestion Unit K-35, KjelFlex K360, Büchi). Concentrated sulfuric acid and Hg- and Se-free Kjeldahl catalyst tablets (Merck) were used for digestion. Titration was done with 0.05 M sulfuric acid. Individual urine volumes and an assumed specific gravity of urine of 1.020 g/mL were used to convert the nitrogen content into grams of nitrogen per 24 hours. The reference range for the specific gravity of urine is between 1.010 and 1.030 g/mL. The Karlsruhe Metabolomics and Nutrition (KarMeN) cohort [40] was used as the reference population.

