#### Sodium and Potassium Content

Sodium and potassium measurements were performed in an accredited clinical laboratory (MVZ Labor PD [name] and colleagues) using ion-sensitive electrodes.

In order to obtain the excreted urinary sodium and potassium amount per day, the respective concentrations (mmol/L) were converted into g/d while taking the volume of urine and the respective molar masses into account.

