## Discussion

### Principal Findings

Within the study, 117 participants completed the recruitment. After the subtraction of some errors in sample collection and measurements, 106 stool samples are available with corresponding data on common nutrition (30-day FFQ). In addition, 109 face-to-face 24-hour recalls were conducted (data on current nutrition), with corresponding urine samples and measured urine parameters. For 82 of these data sets, additional data on physical activity have been collected.

The 2 main aims of the study were to collect samples and data for (1) validating the dietary recall software GloboDiet and (2) for studying the association between diet and the intestinal microbiome. The 117 participants who successfully completed the study were equally distributed with respect to sex and age groups. However, the fraction of participants with a BMI above 25 kg/m² was lower in the study (females: 18/61, 29.5%, males: 27/56, 48.2%) than observed in the official representative statistics of the German population in 2017 (females: 43.1%, males: 62.1%, data set 12211-9018 in the Genesis database [44]). In addition, the average level of education is high in the study population. Therefore, the study population could be somewhat biased toward a healthier lifestyle, including nutrition and activity, than would be expected in the general population.

For the validation of the updated GloboDiet version, protein and potassium intake determined with the software will be compared with the excretion of protein and potassium in the 24-hour urine collection. In addition, EI calculated from the 24-hour recall will be compared to TEE and RMR. To estimate the validity of the current GloboDiet version, different methods will be applied, like the Wilcoxon-signed rank test to test if the differences between nutrient excretion and nutrient intake, as well as TEE and EI, are different from zero, Spearman rank correlation coefficients to assess the strength of the correlations, as well as Bland-Altman plots [45,46]. Bland-Altman diagrams are suitable for visualizing measurement differences. In addition, participants will be grouped into tertiles to assess the agreement in ranking participants regarding nutrient intake and excretion, as well as EI and TEE. Furthermore, for EI, cutoff values according to Goldberg et al [47] and Black [48] will be calculated for group levels as well as for individuals.

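### Urine collections of 20 to under 24 hours can be accepted, but the stated conversions to daily nitrogen, sodium and potassium contain no term for collection time

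*Protocol article*

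**What the plan says.** Four parts of the protocol article bear on this.

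- **Acceptance (Methods, 24-Hour Urine Collection).** Samples are excluded for collection errors, for instance "if the collection time was interrupted, incomplete, or less than 20 hours", or when the first morning urine was not discarded. Creatinine serves as a completeness check, but the article says "it is only suitable for a rough estimate of the completeness of the 24-hour urine collection". It gives no creatinine cutoff and no rescaling.
- **Nitrogen (Nitrogen Content).** Individual urine volumes and a fixed specific gravity of 1.020 g/mL "were used to convert the nitrogen content into grams of nitrogen per 24 hours".
- **Electrolytes (Sodium and Potassium Content).** Concentrations in mmol/L "were converted into g/d while taking the volume of urine and the respective molar masses into account".
- **Use (Discussion, Principal Findings).** The article plans that "protein and potassium intake determined with the software will be compared with the excretion of protein and potassium in the 24-hour urine collection". A Wilcoxon signed-rank test is to be used "to test if the differences between nutrient excretion and nutrient intake, as well as TEE and EI, are different from zero", along with Spearman correlations, Bland-Altman plots and agreement of tertiles.

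**The concern.** The acceptance rule and the conversions do not fit together. A floor of 20 hours has a purpose only if collections between 20 and 24 hours can be kept. The conversions then label whatever was collected as a full day's excretion.

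The recall covers the whole of the previous day, so the two sides of the comparison may span different lengths of time. A short collection lowers the biomarker and pushes intake minus excretion upward. That can hide under-reporting in GloboDiet or suggest over-reporting that is not there. The signed-rank test and the Bland-Altman mean difference depend directly on the absolute level of excretion. Differences in duration between people also add scatter unrelated to diet, which affects the correlations, the tertile agreement and the width of the limits of agreement. If everyone collected for the same number of hours, the rank-based measures would be untouched and only the level would shift.

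**Working it through.** The article states no figure for this error, so there is nothing to reproduce. The check is direct arithmetic.

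**Inputs**
- Minimum accepted duration: 20 h (24-Hour Urine Collection).
- Nominal duration: 24 h (same section).
- Conversion inputs for nitrogen: volume and specific gravity 1.020 g/mL, with a stated reference range of 1.010 to 1.030 (Nitrogen Content).
- Conversion inputs for sodium and potassium: concentration, volume and molar mass (Sodium and Potassium Content).
- Accepted urine collections: 109, with no durations given (Results).
- Assumption, not in the article: excretion runs at a constant rate over the day.

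**Step 1: error in one collection.** If a collection of h hours is reported as a daily amount without scaling, the relative error is h/24 - 1 and the correcting factor is 24/h.

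| Hours | Error in excretion (h/24 - 1) | Factor (24/h) |
|---|---|---|
| 20 | -16.7% | 1.200 |
| 21 | -12.5% | 1.143 |
| 22 | -8.3% | 1.091 |
| 23 | -4.2% | 1.043 |
| 24 | 0 | 1.000 |

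At the 20 h limit the ratio of intake to excretion is inflated by 24/20 - 1 = 20%.

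**Step 2: error in the group mean.** This depends on how many collections were short and by how much, which the article does not report. Purely as an assumed range, let a share s of collections be short and the rest last exactly 24 h, with the same average excretion in both.

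| Share short (assumed) | All at 20 h: s × 4/24 | Spread evenly over 20 to 24 h: s × 2/24 |
|---|---|---|
| 10% | -1.7% | -0.8% |
| 25% | -4.2% | -2.1% |
| 50% | -8.3% | -4.2% |
| 100% | -16.7% | -8.3% |

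If almost all collections were close to 24 h, the group error is close to zero.

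**Step 3: comparison with a factor the article does discuss.** Replacing 1.020 by the ends of the stated specific gravity range changes nitrogen by 1.020/1.010 - 1 = 0.99% and 1.020/1.030 - 1 = -0.97%, so about 1% either way. A collection only one hour short has about four times that effect.

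**The case against.** The best defence is that the article condenses a fuller protocol. It refers to standard operating procedures for sample collection and preparation, and scaling to 24 hours is the kind of one-line step such a procedure might hold. The conversion sentences name inputs without saying that the list is complete, and a result expressed per day is compatible with volumes that were already scaled. There are also safeguards: interrupted and incomplete collections are dropped, participants are asked about difficulties, and creatinine gives a rough check. The Results describe the 109 accepted samples as collected over 24 hours.

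Part of this stands. A time correction may exist in a document not shown, and nothing shows that any accepted collection was materially short. But the article does more than stay silent: it sets out what goes into each conversion, including a specific gravity term worth about 1%, and time is not there. If every collection under 24 hours counted as incomplete, the 20-hour limit would be redundant. The Results wording is a label and gives no durations. Creatinine, by the article's own account, is too rough to replace a time correction.

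Three stronger readings are tempting, and the documents do not support them.
- **Excretion in the study is understated by 17%.** That figure belongs to a single collection at the 20 h limit. The group bias is unknown, and so is its sign if some collections ran over 24 hours.
- **Over-long collections were kept.** No upper limit is stated, but the exclusion reasons are given as examples, so a missing limit is weak evidence.
- **Volume is the only input.** Specific gravity and molar mass also enter. The gap is collection time.

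**Conclusion.** The point holds as a mismatch between a rule that admits collections of 20 to under 24 hours and conversions that, as stated, treat each one as a full day. For an individual the error is h/24 - 1, at most -16.7% for an accepted short collection, assuming constant excretion. For the group the size cannot be determined from the article and may be small. The conclusion also rests on following the conversions as written; a scaling step in an unseen procedure would remove the concern once it is stated. The correction is worth making because the validation tests the absolute difference between intake and excretion.

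**What to change.** 1. Multiply each nitrogen, potassium, sodium and creatinine amount by 24 divided by the recorded collection hours before any comparison with intake, and state this under Nitrogen Content and under Sodium and Potassium Content. If it was already done, say so there.
2. Report the distribution of collection times for the accepted samples.
3. Add a sensitivity analysis restricted to collections close to 24 hours. The scaling assumes a constant excretion rate, and the uncollected hours may hold more or less than the average, so this shows whether the result depends on that assumption.

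The cost is one multiplication per participant and one extra run of the planned comparisons. No new data should be needed, since the 20-hour rule could not have been applied without durations. The downside is small: the scaled value can be slightly wrong when excretion varies over the day, and the restricted analysis uses fewer participants.

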### Stool Sampling and Storage

Study participants were provided with a prepacked stool collection kit (“Easy Sampler,” GP Medical Devices A/S) and received precise oral instructions and a written manual for the sampling procedure. Each participant collected 2 independent, approximately nut-sized samples from the same stool. Samples were frozen at –20 °C immediately after collection, delivered frozen to the study center, and then stored at –80 °C until aliquoting. After all the samples were collected, multiple aliquots of 200 mg and 500 mg were kept at –80 °C until further analysis. One aliquot per sample was immediately transferred to and frozen in NucleoSpin Bead Tubes Type A (Macherey-Nagel GmbH & Co) for DNA extraction (see Microbiome Analysis).

### Analysis of Biomarkers in Urine

#### Overview

The validation of the German GloboDiet version will use an approach with nitrogen and potassium urinary excretion as biochemical markers for protein, as well as potassium intake [36,37]. Nitrogen and potassium excretion were chosen because errors are likely to be independent between the measurements of biomarkers and dietary intake [38,39].

#### Nitrogen Content

Total urinary nitrogen was quantified by the Kjeldahl method using automated digestion and distillation units (Digestion Unit K-35, KjelFlex K360, Büchi). Concentrated sulfuric acid and Hg- and Se-free Kjeldahl catalyst tablets (Merck) were used for digestion. Titration was done with 0.05 M sulfuric acid. Individual urine volumes and an assumed specific gravity of urine of 1.020 g/mL were used to convert the nitrogen content into grams of nitrogen per 24 hours. The reference range for the specific gravity of urine is between 1.010 and 1.030 g/mL. The Karlsruhe Metabolomics and Nutrition (KarMeN) cohort [40] was used as the reference population.

#### Sodium and Potassium Content

Sodium and potassium measurements were performed in an accredited clinical laboratory (MVZ Labor PD [name] and colleagues) using ion-sensitive electrodes.

In order to obtain the excreted urinary sodium and potassium amount per day, the respective concentrations (mmol/L) were converted into g/d while taking the volume of urine and the respective molar masses into account.

#### Osmolality

Osmolality in urine was measured using the freezing point osmometer, Advanced Osmometer Modell 2020 (Advanced Instruments LLC), and values were expressed in mOsm/kg. These values can be used as reference values for potential urinary analytes to be measured in the future.

### Analysis of Stool Samples (Intestinal Microbiome)

Single aliquots of the 2 independent stool samples collected from each subject were used for DNA extraction using the NucleoSpin DNA Stool Kit (Macherey-Nagel). The 200 mg of stool, previously transferred to the bead tubes, were incubated with 850 µL lysis buffer at 70 °C for 5 minutes. A bead beating step was included using a FastPrep 24 machine (MP Biomedicals) at 6.0 m/s for 40 seconds, followed by washing and elution according to the kit’s standard protocol. The purity and concentration of the extracted DNA were checked on a NanoDrop microvolume photometric device. The variable region V4 of the prokaryotic 16S rRNA gene was amplified in a single polymerase chain reaction (PCR) step with dual indexing primers as described by Kozich et al [41] with a modification to increase sensitivity toward Archaea [42] (Multimedia Appendix 1). Phusion Hot Start II DNA Polymerase (Thermo Fischer Scientific) was used in a 25 µL reaction mix with 1 ng template DNA, 0.5 µM of each PCR primer (forward and reverse), 0.2 mM dNTP mix, 0.25 µL enzyme, and 5 µL 5x HF buffer. The PCR program included initial denaturation for 2 minutes at 98 °C, 25 cycles of 30 seconds at 98 °C, 10 seconds at 55 °C, and 15 seconds at 72 °C, followed by terminal elongation for 5 minutes at 72 °C. PCR products were purified using magnetic beads (Mag-Bind RXNPure Plus, Omega) and their concentration was measured using a Quantus Fluorometer (Promega) with the QuantiFluor One dsDNA System (Promega), according to the manufacturer’s recommendation. The PCR products were pooled at an equimolar concentration in 2 independent libraries that were subsequently sequenced on the Illumina MiSeq platform using a MiSeq Reaction Kit v3 with 2 × 301 cycles at a final concentration of 8 pM, adding 20 mol% of PhiX DNA.

### Sample Size Calculation

The sample size was based on the validation of the 24-hour recalls using the difference between energy expenditure (EE) and energy intake (EI) as the end point. The statistical power for a paired *t* test of the hypotheses H_0_: EI – EE = 0, H_1_: EI – EE ≠ 0 was calculated by the Leibniz Institute for the Social Sciences (GESIS) in Mannheim, Germany. Statistical parameters were estimated using data from a study by Biltoft-Jensen et al [43], as this study used comparable methods for the estimation of EE and nutrient excretion. For an effect size *d* = (EE – EI)/SD (EE – EI), significance level α=.05, and group sizes of 50 female and 50 male participants, the statistical power was calculated to be >0.998. To prevent an age bias, the group sizes were distributed evenly to the 3 age groups, that is, recruiting at least 17 participants per sex and age group.

The second aim of the study, the analysis of microbiome composition and its association with nutrition, is exploratory and not hypothesis-driven. Therefore, no additional power or sample size calculations were required for this part of the study.

### Ethics Approval

The study has been performed in accordance with the Declaration of Helsinki. It was approved by the Ethics Committee of the State Medical Chamber of Baden-Württemberg (EK LÄK BW; F-2018-055) in October 2018 and registered at the German Clinical Trials Register (DRKS00015216). All participants were informed in detail about the purpose of the study, examination procedures, measurements, and potential risks involved. Participants signed their consent to the procedures and the analysis of pseudonymized data, including their potential use for research related to nutrition and health. Privacy and confidentiality of personal data are guaranteed by following the regulations of the State Medical Chamber and the EU General Data Protection Regulation. Pseudonymization was achieved by assigning randomized subject identifiers. All participants received €50 (US $56.50) in compensation upon inclusion in the study.

## Results

Recruitment of potential participants involved an initial telephone screening of 230 people who were interested in participating, of whom 133 were selected based on exclusion criteria (Figure 2). After their assignment to the study, 16 subjects had to be excluded for various reasons (Figure 2). Overall, a total of 117 participants completed the 2 visits to the study center (Table 1, Multimedia Appendix 2).

For 109 participants (57 women and 52 men), food consumption and nutrient intake data, assessed by a face-to-face 24-hour dietary recall, are available. The participants were equally distributed among the age groups (18-39 years of age: 36; 40-59 years of age: 35; 60-79 years of age: 38). Urine samples collected during a 24-hour period were provided and suited for analysis in 109 cases (nitrogen and osmolality measurements failed in 2 cases that could not be validly reproduced).

ActiHeart records were not complete in 27 cases, mostly because of the detachment of the device or similar technical problems that resulted in measurements shorter than the required 24 hours. Physical activity data were obtained for 82 of the 109 participants for which urine and current food consumption data were collected.

Nearly all participants provided the requested stool samples, but a few reported irregularities during sampling (eg, potential contamination with toilet water) that led to the exclusion of the samples from further analyses. A final available number of 111 stool samples, each consisting of 2 replicates, were attained.

FFQs were completed by 106 participants (53 women and 53 men) who also provided valid stool samples, equally distributed over the age groups (18-39 years of age: n=37; 40-59 years of age: n=31; and 60-79 years of age: n=38).

**Table 1 table1:** Study population characteristics (N=117).

Characteristics		Female participants, n (%)^a^	Male participants, n (%)^a^
